### Statistical analysis

Descriptive statistics will be used to present feasibility indicators and baseline sample characteristics at M1, including means (standard deviations) for normal data and, median (interquartile range) for non-normal data Differences in baseline characteristics between the intervention versus control arm, stratified by age-range of ALHIV (10–14 years. vs. 15–19 years) will be assessed using a chi-square test for categorical variables and Kruskal-Wallis *H* test for continuous variables. Baseline variables that differ between groups will be included as covariates in the regression analysis. To compare primary outcomes, we will analyse wellbeing score change at M1 and M5 between arms using linear regression. Furthermore, we will explore changes in scores between M2 and M5. To include all participants in the primary analysis (intention to treat analysis), we will perform multiple imputation methods if the loss of those missing from follow-up is significant, and assumptions are met. Participants who complete the questionnaire at baseline (M1) and endline (M5) will be included as per protocol. All statistical analyses will be performed using Stata (Stata Corp, College Station, TX, V17) (see Table 2 for participant timeline).

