### Design

This will be a two-group parallel, open label pilot RCT. The study will have two arms, an intervention group (*n* = 50) and a control group (*n* = 50).

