### Randomisation and allocation concealment

A statistician on the research team who is not involved in the intervention or outcome measure assessments will randomly allocate participants to the intervention or control group. The randomisation list will be generated in STATA (Stata Corp, College Station, TX, V17) using block randomisation techniques. This method is used to ensure a sample size balance across groups over time. Blocks will be small and balanced with predetermined group assignments, which keeps the numbers of subjects in each group similar. A seed will be used for the reproducibility of the same randomisation output obtained. Block randomisation with randomly selected block sizes of 2, 4, 8, and 12 will be generated. Four blocks of equal size (*n* = 25) will be generated in STATA, with two blocks assigned to each study arm (i.e. intervention: n=2 × 25 = 50; control: *n* = 25 × 2 = 50) and the list exported to Excel. This list will be emailed to a second researcher who will assign the intervention or control programme to each participant.

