### Sample size

Our primary outcome is pre-post between difference in caregiver wellbeing scores. Assuming a mean caregiver wellbeing VAS score of 6.5 in M1 versus 8.5 in M5 (SD1.9) in the intervention arm, we would need a minimum sample size of *n* = 15 per arm to have 80% power to detect a treatment effect of between δ = 0.6–0.5 [66, 70]. Thus a sample size of *N* = 100 will satisfy this primary outcome and give us enough sample to look at feasibility measures (consent and retention rate ≥ 80%), assuming *n* = 20 refuse to participate or are lost to follow-up.

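### Between-arm baseline tests choose the covariates for the primary wellbeing regression, so the model is not fixed in advance; separately, it has no fixed term for baseline wellbeing

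*Protocol article*

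**What the plan says.** All of this stands in the protocol article. Under Statistical analysis, baseline differences between arms, stratified by the age range of the adolescent (10–14 or 15–19 years), "will be assessed using a chi-square test for categorical variables and Kruskal-Wallis *H* test for continuous variables". The next sentence turns the results into a model: "Baseline variables that differ between groups will be included as covariates in the regression analysis". The primary comparison follows: "we will analyse wellbeing score change at M1 and M5 between arms using linear regression".

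The section names no covariate that is always included. It gives no threshold for a difference and no count of variables to be tested. It does not say how results from the two age strata combine into a decision to include.

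Under Randomisation and allocation concealment, "The randomisation list will be generated in STATA (Stata Corp, College Station, TX, V17) using block randomisation techniques"; no stratification factor is given. The Design section plans 50 participants per arm, and Sample size allows for 20 of the 100 who "20 refuse to participate or are lost to follow-up".

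**The concern.** If allocation works as intended, the arms differ at baseline only by chance. A test of that difference says nothing about whether a variable predicts wellbeing, and prediction is what makes a covariate worth including. The rule can therefore admit variables unrelated to the outcome and leave out related ones that happen to be balanced. Because the threshold and the role of the age strata are open, two analysts could apply the same sentence and fit different primary models.

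A second weakness sits beside the first. A change score uses baseline wellbeing with its coefficient fixed at 1, which is less precise than estimating that coefficient whenever the baseline–endline correlation is below 1. The selection rule is the only route by which a baseline term could enter.

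What is at stake is the precision of the between-arm wellbeing difference, which is listed first among the primary objectives, and the power calculation for a large trial, which is a secondary objective.

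**Working it through.** **The plan's own figure.** Sample size states: "Assuming a mean caregiver wellbeing VAS score of 6.5 in M1 versus 8.5 in M5 (SD1.9) in the intervention arm", leading to 15 per arm for 80% power. With two-sided 5% (assumed, as the article gives no alpha), n = 2 × (1.960 + 0.842)² × (1.9/2.0)² = 14.2, rounded up to 15 per arm. The figure reproduces from those means and SD. It does not follow from the standardised effect of 0.5 to 0.6 in the same sentence, which would need 63 or 44 per arm. That is a separate matter. The effect of 0.5 SD used below is the lower end of the plan's range.

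**Inputs.** From the article: 50 per arm; 20 losses, hence (100 − 20)/2 = 40 per arm analysed; the selection rule; the change-score outcome. Assumed: k = 5 to 20 independent tests, a 5% threshold, baseline wellbeing among the variables tested, equal SD at both time points, and baseline–endline correlation ρ = 0.3 to 0.7. The article gives none of these.

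**Chance inclusion.** P(at least one) = 1 − 0.95^k.

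- k = 5: 23%
- k = 10: 40%
- k = 15: 54%
- k = 20: 64%
- 20 variables tested in both age strata, either able to trigger inclusion: 1 − 0.95^40 = 87%

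Correlated variables would change these figures, and income, food insecurity, depression and stigma are unlikely to be independent.

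**How often baseline wellbeing enters.** With one test at 5%, it enters in 5% of trials. If either age stratum can trigger inclusion, the figure is 1 − 0.95² = 9.75%. With one test at a 10% threshold it is 10%. Both departures together would give 1 − 0.90² = 19%, so it would still be left out in about four trials in five.

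**Precision.** With unit SD at each visit, the change score has variance 2(1 − ρ) and the baseline-adjusted outcome 1 − ρ². The ratio is 2/(1 + ρ). Power is Φ(0.5/SE − 1.960), where SE = √(2/40) × SD.

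| ρ | Variance ratio | Power, change score | Power, baseline-adjusted | Simulated power under the rule |
|---|---|---|---|---|
| 0.3 | 1.54 | 47% | 65% | 46% |
| 0.5 | 1.33 | 61% | 73% | 62% |
| 0.7 | 1.18 | 82% | 88% | 80% |

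The loss is 6 to 18 percentage points. With no losses (50 per arm) the pairs are 56% and 75%, 71% and 82%, 90% and 94%.

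**Simulation of the rule.** The setting was 40 per arm, baseline wellbeing plus nine independent variables unrelated to outcome, Kruskal-Wallis p < 0.05, and 2,000 runs per setting, without age strata. At least one variable entered in 38% to 41% of runs, and baseline wellbeing in 4.2% to 4.8%. Type I error was 3.9% to 5.4%. A second simulation with 20 variables (4,000 runs) gave type I error of 4.4% and a mean of 0.99 variables selected. Applied mechanically, the rule recovers almost none of the gain from baseline adjustment and does not raise the overall false-positive rate.

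**The case against.** Several points on the other side stand.

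- **The tests do not cause the precision loss.** It comes from a change score without a baseline term and would be the same if the selection rule were deleted and nothing else changed. The rule's own cost in degrees of freedom is about one spurious covariate among 80 participants, which is trivial. What the rule itself does is leave the model open.
- **Baseline wellbeing is not ignored.** A reader might infer that the plan usually omits the strongest predictor. The article does not identify the strongest predictor, and the change score already carries baseline with coefficient 1. Only the remaining association is lost: the correlation of baseline with change is −√((1 − ρ)/2), or −0.5 at ρ = 0.5.
- **This is a pilot.** The Progression criteria are retention and enrolment of at least 80%, and neither uses the wellbeing estimate.
- **A baseline comparison can serve as a process check.** Piloting randomisation is an objective, and the randomisation section describes both random block sizes of 2, 4, 8 and 12 and four blocks of 25, which do not fit together. Banning every baseline comparison would go too far.

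A further objection does not succeed: that a separate analysis plan may settle the covariates. It may, but the point concerns a rule that the article states, not a detail left out.

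**Conclusion.** The point holds in two parts. First, the article selects covariates for the primary regression by testing chance imbalance, so the model is not fixed in advance. At least one chance inclusion is expected in 23% to 64% of trials for 5 to 20 independent tests at 5%. The 87% figure applies only if 20 variables are tested in both strata and either can trigger inclusion; under that reading baseline wellbeing enters in about 10% of trials, not 5%. Second, the change-score model has no fixed baseline term, and the rule supplies one in only about 5% to 10% of trials. The variance is then 1.18 to 1.54 times that of the adjusted model for ρ from 0.7 to 0.3.

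Two stronger readings are not supported. A reader might infer that the rule produces false positives, but simulated type I error stays near 5%. Any further effect of discretion over the open threshold cannot be sized from the article. A reader might also link the fault to the open-label design or the late registration; neither bears on how covariates should be chosen.

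The change should be made, but no stated progression decision depends on it. The sizes rest on the assumed ρ, number of tests and threshold; the existence of the rule does not.

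**What to change.** In Statistical analysis:

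1. Remove the sentence that makes baseline differences the criterion for covariates.
2. Name the baseline CarerQol score, on the same scale as the outcome, as a covariate in the primary regression whatever the baseline comparison shows. Adolescent age group (10–14 or 15–19 years) may be added, since the plan already uses it.
3. Present baseline data by arm descriptively. If a baseline check is kept, label it as a check on the randomisation process with no role in model choice.
4. Report adjustment for imbalanced variables as a labelled sensitivity analysis.

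Trial status says that follow-up is complete and analysis is under way. The change should therefore be dated, with a statement of whether outcomes by arm had been seen when it was made. If they had, the report should say so beside the revised model.

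The cost is a few sentences, one degree of freedom for the baseline term (one more if age group is added), and the freedom to choose covariates after seeing the data. No new data are needed, because baseline wellbeing is already needed for the change score.

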### Setting

This study will be conducted in a peri-urban community within the south of the eThekwini municipality, KwaZulu-Natal, South Africa. Recruitment, baseline quantitative assessments, and qualitative interviews will be conducted face-to-face. Whereas intervention delivery and end of trial assessments will be conducted telephonically.

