#### Primary clinical outcome measures informing our sample size

Percentage change in wellbeing scores pre-vs. post-intervention:*Wellbeing* will be measured using the Care-related Quality of Life (CarerQol) instrument. The CarerQol instrument is a preference-based measure that was developed for use in economic evaluations [64], and has exhibited moderate construct validity (correlation co-efficient with CarerQol and self-rated burden dimensions ranging from 0.2 to 0.4) among older carers in the Netherlands [65]. Clinical and convergent validity have also been supported [66].Successful consent rate: a minimum of ≥ 80% of eligible participants enrolled in the studySuccessful retention rate: a retention rate of ≥ 80% of recruited participants

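### The wellbeing outcome is a percentage change in one section and a score difference in the others, and the baseline score enters the model only if the arms happen to differ on it

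*Protocol article*

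**What the plan says.** The protocol article defines the wellbeing outcome in four places.

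- **Primary objectives:** the first objective is a difference in wellbeing scores, baseline against endline, compared between arms.
- **Primary clinical outcome measures informing our sample size:** "Percentage change in wellbeing scores pre-vs. post-intervention".
- **Sample size:** "Our primary outcome is pre-post between difference in caregiver wellbeing scores". The inputs are in points: "Assuming a mean caregiver wellbeing VAS score of 6.5 in M1 versus 8.5 in M5 (SD1.9) in the intervention arm". The section then gives a "minimum sample size of *n* = 15 per arm to have 80% power to detect a treatment effect of between δ = 0.6–0.5".
- **Statistical analysis:** "we will analyse wellbeing score change at M1 and M5 between arms using linear regression".

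On covariates, the Statistical analysis section tests baseline characteristics between arms (chi-square or Kruskal-Wallis) and then states: "Baseline variables that differ between groups will be included as covariates in the regression analysis". The baseline wellbeing score is not named as a covariate in its own right.

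**The concern.** Two things look wrong.

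First, the outcome list and the other three sections do not describe the same quantity. A gain of 2 points is 50% from a baseline of 4 and 25% from a baseline of 8, so percentage change weights low-scoring caregivers more heavily. It has no value at a baseline of 0. The heading of the outcome list says its measures informed the sample size, but the calculation uses points. The trial is open label, and the Trial status section says analysis is under way. An unresolved choice between two outcome definitions therefore leaves room to choose after seeing the data.

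Second, baseline wellbeing is collected from everyone and is an obvious predictor of endline wellbeing. The plan lets it into the model only through a rule based on observed differences. Under randomisation such differences arise by chance, so the rule selects on chance rather than prognostic value. In most realisations it would leave the score out and forgo precision that costs nothing.

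**Working it through.** **1. The plan's own figure.** Inputs from the Sample size section: difference 8.5 − 6.5 = 2.0 points, SD 1.9, 80% power. Two-sided α = 0.05 is assumed, since none is stated.

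n per arm = 2 × (1.96 + 0.84)² × (1.9/2.0)² ≈ 14.2, so 15. The stated 15 reproduces (16 by t test).

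The section does not say whether 1.9 is the SD of a score or of a change. The two coincide at ρ = 0.5, because the change-score variance 2σ²(1−ρ) then equals σ².

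The figure is therefore in VAS points; nothing in it uses a percentage. The standardised effect it implies is 2.0/1.9 = 1.05, not the 0.5–0.6 in the same sentence. That mismatch is a separate point, but both effect sizes are used below because the plan states both.

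**2. Precision with and without the baseline score.** Let σ be the score SD, equal at baseline and endline, and ρ the correlation between the two. The documents give no ρ, so a range is shown.

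- Unadjusted change: variance 2σ²(1−ρ)
- Adjusted for baseline: variance σ²(1−ρ²)
- Ratio, adjusted to unadjusted: (1−ρ²) / [2(1−ρ)] = (1+ρ)/2

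The Sample size section allows for 20 of 100 refusing or being lost, which leaves 40 per arm if losses are equal. Power is Φ(δ√(n/2)/s − 1.96), where s is the SD in units of σ: √[2(1−ρ)] or √(1−ρ²).

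Worked case, δ = 0.5, ρ = 0.5, n = 40:

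- Unadjusted: s = 1, 0.5 × 4.472 = 2.236, Φ(0.276) = 61%.
- Adjusted: s = 0.866, 2.236/0.866 = 2.582, Φ(0.622) = 73%.

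| ρ (assumed) | Variance ratio | Power, δ = 0.5: unadjusted / adjusted | Power, δ = 0.6 | Power, 2 points (δ = 1.05) |
|---|---|---|---|---|
| 0.3 | 0.65 | 47% / 65% | 62% / 80% | 98% / >99% |
| 0.5 | 0.75 | 61% / 73% | 77% / 87% | >99% / >99% |
| 0.7 | 0.85 | 82% / 88% | 93% / 96% | >99% / >99% |
| 0.8 | 0.90 | 94% / 96% | 99% / 99% | >99% / >99% |

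**3. Percentage change.** This was simulated with assumed inputs: integer scores clipped to 0–10, baseline mean 6.5, SD 1.9, a 1-point effect (close to 0.5 × 1.9 = 0.95) and 40 per arm. The scale range is not in the documents. Power for percentage change, point change and baseline-adjusted analysis was about 32%, 48% and 66% at ρ = 0.3; 42%, 60% and 73% at ρ = 0.5; and 63%, 80% and 87% at ρ = 0.7. About 6% of simulated trials had at least one baseline of 0. Percentage change and point change disagreed on significance in roughly one trial in five.

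**4. Change or endline as response.** Change is endline minus baseline. Once baseline is a covariate, subtracting it from the response shifts only the baseline coefficient, by exactly 1. The arm coefficient and its standard error are identical, so the plan can keep change as the response.

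**The case against.** Several stronger readings are tempting, and the documents do not support them.

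- **No baseline adjustment at all.** A reader might infer this from the model sentence alone. The sentence before it admits baseline variables that differ between arms, and the wellbeing score could enter that way. Adjustment is conditional, not absent.
- **An underpowered or invalid analysis.** An unadjusted change score in a randomised comparison is valid, only less efficient. At the 2-point planning difference, power is about 98% or more either way. The loss matters at the effects of 0.5–0.6 that the same section names, and mainly if ρ is low. No ρ is given.
- **A choice between two CarerQol scores.** The outcome list says "The CarerQol instrument is a preference-based measure that was developed for use in economic evaluations" and the sizing uses a VAS score, so one might infer competing scores. The article does not describe the instrument's components. All that can be said is that the VAS is named only in the Sample size section.
- **Bias from the change of interview mode.** Baseline is face-to-face, while "intervention delivery and end of trial assessments will be conducted telephonically". This applies to both arms, and the planned contrast is between arms. No section proposes to read within-arm change as the treatment effect.

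It is also fair to say that percentage change appears once and no analysis of it is described; that this is a pilot whose progression criteria rest on enrolment and retention; and that covariate detail often sits in an analysis plan not shown here. These points lower the severity. They do not remove the contradiction, which is in a list headed as primary. Nor do they excuse the covariate rule, which the article itself states.

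**Conclusion.** The point holds in two parts.

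The outcome definition is wrong as written: one section says percentage change, while the objective, sizing and analysis say a between-arm difference in score or score change. The sizing supports only the version in points. That percentage change is less efficient rests on the simulation's assumed 0–10 scale; that it is undefined at a baseline of 0 does not.

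Prespecifying the baseline score is a free improvement. Against the unadjusted change score that results when the rule leaves it out, it cuts variance by 10% to 35% for ρ from 0.8 to 0.3. At δ = 0.5 with 40 per arm, the gain in power is about 18 percentage points at ρ = 0.3, 12 at 0.5 and 6 at 0.7. This assumes equal SDs at both times, two-sided α of 0.05 and equal losses. At the 2-point difference the gain is immaterial.

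This should be fixed; it does not threaten the validity of the trial.

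**What to change.** 1. In the outcome list, delete the word percentage and state the measure as the between-arm difference in change in the wellbeing VAS score from M1 to M5, in points. This is the score used for sizing, and it should be the single wellbeing outcome.
2. In the Statistical analysis section, include the M1 VAS score as a prespecified covariate whatever the observed imbalance. For this variable, that replaces selection by baseline differences. Either change or the M5 score may be the response.
3. Since analysis is already under way, record the clarification with its date and say whether outcome data by arm had been seen.

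The cost is one word deleted, one outcome sentence reworded and one covariate added. No new data, participants or assessments are needed.

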**Table 2 Tab2:**
[figure not shown]
Participant timeline

### Progression criteria

The following criteria must be met in order to consider progression to a main RCT:A retention rate of ≥ 80% of recruited participantsA minimum of ≥ 80% of eligible participants enrolled in the study

## Discussion

The aim of this pilot randomised trial is to compare the feasibility and preliminary effectiveness of an economic incentive package (cash + motivational SMS) versus a control for improving caregiver wellbeing. package. The results from this pilot trial will provide the critical data to determine whether a larger-scale RCT is warranted and feasible. This intervention represents an integrated approach, specifically designed to target aspects that matter to caregiver’s wellbeing in this setting (such as financial problems, mental health, relational problems, support, physical health) [14]. It is designed to be delivered remotely by lay counsellors and thus allows access to care for a vulnerable group who otherwise may not be able to receive such care due to time, transport limitations, lack of state psycho-social support services, along with the national social limitations implemented due to the COVID-19 pandemic.

Through this intervention we will investigate whether a cash incentive of three cash payments (of ZAR 350, approximately 23 USD) over a 3-month period, coupled with positive or affirmatory short messages, will have a positive influence on caregiver wellbeing. Several trials have shown that financial incentives are effective in improving HIV testing, including adherence to treatment and clinic appointments [34, 35], and have been linked to improvements in quality of life [36]. Offering a financial incentive may also help in overcoming caregiver present- and loss-averse biases by offsetting immediate opportunity costs linked to health-behaviour change, and uncertain and delayed gains [37, 38]. Additionally, the cash incentives could potentially improve their quality of life by providing them with resources to meet their personal care needs and the monetary resources needed to plan and meet their caregiver and household responsibilities [31, 39]. More importantly, it could serve as recognition for the indispensable care they provide, thereby intensifying their sense of responsibility and quality of care provided to ALHIV. The SMSs that will accompany each cash payment will serve as a nudge to deliver health information and to motivate caregivers to access care and adhere to treatment [45, 46]. Text messages have been shown to be effective in reducing depressive symptoms [43] and promoting uptake of mental healthcare [44]. Furthermore, studies in SSA have shown that SMS reminders sent to caregivers are effective in promoting appointment attendance and medical adherence [47].

In the context of high unemployment and lack of access to psycho-social support services, which have heightened during COVID-19 [25, 26, 71], our intervention could potentially show substantial improvement in carers wellbeing compared to the control arm. Alternatively, our results could show no effect as the COVID-19 pandemic is likely to have had substantial impact on carers mental health and wellbeing [25, 26, 71], requiring a more intensive intervention, targeting multiple levels (individual, household, community). Key ethical concerns of this trial include the need for carers to cover transport costs to commute to a cash withdrawal point to obtain the incentive, safety and security risks on the carer given the dangers of withdrawing cash in high crime informal areas and storing cash within households exposing them to potential GBV and substance abuse. Other ethical considerations include that the motivational SMSs could potentially induce emotional distress and depression as they could make carers more aware of their living conditions and poor mental health status. The loaning or sharing of the cash incentive between carers and delivery of the intervention to carers admitted to hospital or who have passed on could be a key challenge the trial could face.

The RCT will utilise a pre-post study design with a control group, with qualitative and cost data collected alongside the main trial data, which will be used to assess the end user acceptability and the affordability of the intervention. Data from this pilot trial will be used to inform the adaptation of the intervention and evaluation for a larger trial, which will provide robust evidence on the effectiveness and cost-effectiveness of this intervention [72]. We will thus be able to draw on the longitudinal qualitative data to help explain changes in our quantitative measures over time and compare changes to the control group. The intervention draws on the nudge approach and targets three behavioural barriers often targeted by nudges used in health programmes (i.e. aspiration framing, loss aversion and altruism). Furthermore, our evaluation of the intervention addresses some of the current shortcomings of the nudge approach in that it is using a causal design and drawing on qualitative research methods to further explain the patterns observed. Moreover, the cash component of the nudge seeks to address the food and economic insecurity of the household, a key social determinant of wellbeing. This intervention, if further assessed in a larger trial, could provide critical evidence for informing COVID-19 social relief policies which in many parts of SSA have centred around provision of households with cash and very little attention on mental health support. It could provide the data needed to advocate for cash + care programmes for carers as part of future pandemic preparedness.

